**Figure 1 F1:**
[figure not shown]
Study protocol. In the study protocol, subjects will undergo 36 h periods of acute sleep deprivation (ASD). The black arrows indicate the time points of Electro- encephalogram (EEG) recordings and treatment group receive electroacupuncture treatment.

## EEG Recording and ERP Analysis

The subjects will sit comfortably in a quiet room. Continuous EEG recordings will be obtained using Brain Vision recorder software. The sampling frequency will be 1,000 Hz, and the electrode impedances will be maintained below 5 kΩ. The electrodes will be placed according to the international 10–20 system; a total of 32 electrodes will be recorded in this study. ERP component analysis will be performed using Matlab 2018b and will include amplitudes and latencies. EEG data will be analyzed and collected by people who have received professional training.

## Outcomes

### Primary Outcome

The primary outcome is the MoCA score. The cognitive areas assessed include attention and concentration, executive function, memory, language, visual structure skills, abstract thinking, calculation and orientation, with a total score of 30. The lower the score, the more severe the cognitive impairment.

### Secondary Outcomes

The behavioral data and latency and amplitude of N2 and P3 amplitude will be used to evaluate the effect of sleep deprivation and the intervention effect of acupuncture. ERP component detection, such as N2 and P3, has been used for the measurement of brain activity (13) and as a reflection of brain executive function (30–37). The behavioral outcome variables include the mean RT for correct hits, hit rates (correct button presses for Go stimuli), and the percentage of false alarms (FAs, incorrect button presses in response to No-Go stimuli), which are used as indices of individual behavior performance. Executive function and working memory will be assessed with the Wisconsin Card Sorting Test (WCST). Working memory and the Digit Span (DS) of the Wechsler Adult Intelligence Scale (43). The Epworth Sleepiness Scale (ESS), also known as the Epworth Daytime Sleepiness Scale, developed by Johns (44), will be used to evaluate excessive drowsiness during the day. The maximum score on the scale is 24 points, with >6 points indicating drowsiness, >11 points indicating excessive drowsiness, and >16 points indicating dangerous drowsiness. The FS-14 was jointly compiled by a number of experts, including Chalder and Berelowitz, in the United Kingdom (45). The physical fatigue score is obtained by adding the scores of eight items (1–8), the mental fatigue score is obtained by adding the scores of six items (9–14), and the total fatigue score is the sum of physical and mental fatigue scores. The highest score of physical fatigue is 8, the highest score of mental fatigue is 6, and the highest total score is 14. The higher the score, the more serious the fatigue.

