**Methods:**

We will recruit 60 healthy subjects. The participants will be randomly divided into a treatment group, a control group, a sham electroacupuncture group and a blank group, at a 1:1:1:1 ratio. The primary outcome will be determined by the change from baseline to 36 h in the MoCA score. The secondary results include the amplitude and latency of ERP N2 and P3, Go-hit rates, Go-RTs, No-Go-FA rates, the WCST, the Digit Span Subtest of the WAIS, the ESS score and FS-14. The 15 healthy subjects will not receive acupuncture treatment and ASD, but will receive EEG records and cognition functions test at the beginning and end of the experiment. Electroacupuncture intervention will be performed for 30 min once every 12 h, a total of three times. ERP measurements and other tests will be performed after baseline and ASD, and the statistician and outcome evaluator will be blinded to treatment allocation.

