## Visual Go/No-Go Task Design

At the beginning of the visual Go/No-Go task, a small white cross (+) on a black background appears at the center of the screen for 100 ms before each trial, followed by the stimulus. Each stimulus is presented for a duration of 100 ms, with an inter-stimulus interval of 800 ms. The task has two blocks with 150 trials in each block. In one block, the subjects are asked to respond to the left arrow [target stimulus (Go)] and withhold responding to the right arrow [non-target stimulus (No-Go)], while in the other block, the response pattern is reversed. The Go stimuli occur with a one-third probability, and the sequence of Go/No-Go stimuli is pseudorandom to ensure that the No-Go stimuli do not appear in a continuous sequence. The participants will undergo a training session to ensure that they understand the Go/No-Go task and that their performance is above 90%.

The participants will arrive at the lab at 20:00 p.m. and perform a Go/No-Go task as a baseline. They will be asked to ensure that they get a full night's sleep (by wearing a wrist-operated sleep monitor and “sleep log” to ensure that they get at least 8 h of sleep), and the experiment will begin at 8:00 a.m. the next morning, taking the Go/No-Go task as 0 h. The participants will not be allowed to sleep for the next 36 h, during which time they will receive acupuncture every 11 h. After 36 h, the participants will be asked to complete the Go/No-Go task again. They will be accompanied and supervised by 10 staff members, and there will be two emergency doctors and nurses in the laboratory at all times. The participants will be asked to stay in the laboratory and will be allowed to talk, read, play computer games, and engage in other non-strenuous activities. They will not be allowed to smoke or drink coffee, tea, hot chocolate, wine, or other bladder-irritating drinks (Figure 1).

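### The Epworth scale rates usual daytime dozing, so its 36-h score is not a valid or sensitive measure of the sleepiness this trial induces, and no other sleepiness outcome is listed

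*Protocol article*

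**What the plan says.** The Methods part of the abstract in the protocol article lists "the Digit Span Subtest of the WAIS, the ESS score and FS-14" among the secondary outcomes. Under Secondary Outcomes, the ESS is also given its alternative name, which labels it a daytime sleepiness scale, and it "will be used to evaluate excessive drowsiness during the day". The scoring follows: "The maximum score on the scale is 24 points, with >6 points indicating drowsiness", with further bands above 11 and above 16.

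Table 1 marks the ESS at two time points, baseline and 36 h. The abstract agrees: "ERP measurements and other tests will be performed after baseline and ASD".

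The conditions between the two ratings are set out under Visual Go/No-Go Task Design. "The participants will not be allowed to sleep for the next 36 h". On the setting: "The participants will be asked to stay in the laboratory and will be allowed to talk, read, play computer games". On supervision: "They will be accompanied and supervised by 10 staff members". The Blank Group section, by contrast, leaves that arm without any intervention and on its ordinary schedule of work and rest.

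Table 1 and the outcome sections list no other sleepiness rating. The FS-14 is described as a measure of physical and mental fatigue.

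**The concern.** The ESS is built around everyday life: how likely the person usually is to doze in ordinary situations. Repeating it at the end of a period in which ordinary situations and dozing are both ruled out leaves the second answer without a clear reference. One participant may repeat the answer about usual life, which 36 h of laboratory wakefulness need not alter. Another may turn the items into a rating of how sleepy he feels now. The two answers mean different things and go into the same mean.

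Sleepiness is a direct effect of the exposure. The Background treats alertness as something deprivation harms, and it compares acupuncture with caffeine, which it describes as improving alertness as well as cognition. The stated objective is narrower: inhibition control. If electroacupuncture improves MoCA or Go/No-Go performance, a reader will ask whether participants were simply less sleepy. The only outcome that speaks to this is the ESS. A null ESS result could not be read as no effect on sleepiness, and a positive one would be hard to interpret.

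**Working it through.** No figure for the ESS is stated in the article (no expected change, SD or power; the sample size section concerns MoCA only), so there is nothing to reproduce. The check sets the instrument against the schedule.

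1. **Instrument.** The article names the ESS, gives its maximum of 24 and its bands, and labels it a daytime sleepiness scale. It prints neither the items nor the reference period. That the items ask about usual dozing in everyday situations is taken as the defining content of the named instrument; it fits the daytime label.

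2. **Timing.** Table 1 gives two ratings, at baseline and 36 h. The interval between them is not fixed beyond doubt. The task-design section describes a baseline Go/No-Go task at 20:00, a night's sleep, and then a start at 08:00 as 0 h. If the ESS is given at 08:00, the ratings are 36 h apart. If it is given the evening before, they are 12 h + 36 h = 48 h apart, with a night's sleep in between. In either case the second rating comes at the end of 36 h of enforced wakefulness.

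3. **Conditions in the deprived arms.** Sleep is forbidden, participants stay in the laboratory and staff supervise them. Everyday dozing is therefore not available as something to report on for those 36 h.

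4. **Conditions in the blank arm.** The normal routine continues, so these participants can answer at 36 h just as the scale intends.

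5. **Consequence for the comparisons.**
   - Blank versus deprived arms: the contrast mixes a difference in sleepiness with a difference in what the question can mean.
   - Among the three deprived arms: all face the same ambiguity, so randomisation protects the comparison from bias. The loss is in sensitivity and interpretability.
   - Severity bands: they grade habitual sleepiness. Applied at 36 h to confined, sleepless participants, they have no clear meaning.

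6. **Extent.** With 60 participants at 1:1:1:1, each arm expects 60 / 4 = 15, and the three deprived arms 3 × 15 = 45. One of several secondary outcomes is affected.

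**The case against.** The strongest objection is that the decisive premise is not printed in the article. It does not reproduce the ESS items or recall period, and a condensed journal article commonly leaves questionnaire instructions to the full protocol or case report form. An adapted instruction may exist. This stands as a limit, but it does not remove the point. The article makes a positive choice of a named instrument, its standard bands and its time points, and what that instrument asks is what defines it. If an adapted version is used, it should be stated and justified.

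A second objection is that ESS scores may rise after deprivation, because participants may well answer about their current state. This also stands. A reader might infer that the scale cannot change at all over 36 h; the documents do not support that, and the claim here is only that the score is not valid or sensitive for this purpose.

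Other stronger readings should be resisted:
- A reader might try to size the insensitivity from the share of a recall window that 36 h occupies. The article gives no window, and such a share would not measure responsiveness.
- A reader might expect a floor problem because participants are selected on PSQI below 5. PSQI is not an ESS score, and a low baseline leaves room for the rise that deprivation should produce.
- A reader might extend the criticism to the FS-14. Its instruction is not shown, and rewording it to ask about the present moment would be the same kind of improvisation that is at issue with the ESS.

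Finally, a one-item scale in about 15 participants per arm would not prove whether a cognitive gain comes from alertness. That is true. It would give an interpretable sleepiness result, which the present plan does not.

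**Conclusion.** The point holds as a measurement problem in one secondary outcome. The ESS is the only sleepiness outcome, and its 36-h score in the deprived arms is not a valid or sensitive measure of induced sleepiness or of short-term relief. The size cannot be put as a number, because the article gives no ESS change, SD or reference period.

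A reader might infer that the trial's main result is undermined. It is not: the primary MoCA outcome does not depend on the ESS, and neither do the ERP, Go/No-Go, card-sorting and digit-span outcomes.

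The conclusion rests on two assumptions: that the ESS is used in its usual form, and that no momentary sleepiness scale is given outside the listed outcomes. The change is worth making because it is cheap.

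**What to change.** - Add a one-item momentary sleepiness scale (for example Karolinska or Stanford) immediately before the Go/No-Go task at baseline and at 36 h, in all four arms alike, and name it as the sleepiness outcome in place of the ESS.
- Keep the ESS at baseline as a description of the sample. If it is also kept at 36 h, say that this is for comparability with other studies only.
- Do not interpret the bands above 6, 11 and 16 at 36 h.
- State which baseline session the rating belongs to, the evening before or 0 h.

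This needs a new row and an edited ESS row in Table 1, with short changes to the abstract and Secondary Outcomes. The cost is one extra form of under a minute at each administration, and some loss of ESS comparability with other studies, which optional retention at 36 h would limit.

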### Other Outcomes

Participant characteristics such as age, weight, body mass index, blood pressure, heart rate, pulse, liver function, renal function, electrocardiogram, and back pain history will be collected using electronic case report forms.

### Adverse Events

Any adverse event resulting from electroacupuncture in participants, such as headache, nausea, dizziness, localized infections, bleeding, or local subcutaneous hematoma, will be recorded, assessed, and reported. The occurrence time, cessation time duration, correlation with acupuncture, measures taken, and outcomes of adverse events will also be recorded. If serious adverse events occur, the Institutional Ethics Committee of the Third Affiliated Hospital of Henan University of Traditional Chinese Medicine will be informed, and the committee will decide whether to unblind and withdraw from the study.

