## Background

Acute sleep deprivation (ASD) is the elimination of sleep for a period of time (at least 24 h) to significantly prolong wakefulness (1). Inadequate sleep and sleep disorders have become an important public health problem. ASD can effect mood, attention, memory, alertness, cognitive performance and metabolism (2, 3). With the increasing pace of life, the incidence of sleep deprivation has increased significantly, which has attracted attention in the military field and many social sectors (such as aviation, navigation, medical treatment, and transportation). The common negative effects of sleep deprivation include feeling too sleepy during the day, accidents from lack of attention, mood changes, and changes in appetite (4). Insufficient sleep increases the risk of human error-related accidents (5). ASD affects cognition in many ways and can negatively impact alertness, learning, memory, and executive function (6–12). Since ASD has serious effects on human cognitive brain function, safety intervention studies on the effects of ASD, such as acupuncture, are increasingly popular in this field (13, 14).

Studies show that administration of caffeine may improve vigilance, alertness, mood and cognitive processes and enhance cognitive processing related to response selection and inhibition (15, 16). Compared with the central nervous system stimulant caffeine, acupuncture is a safe alternative therapy with minimal side effects (17). A Delphi expert consensus survey (18) shows that more than 80% of experts agree that acupuncture can be used to improve cognitive function, which has been underpinned by the results of previous studies (19, 20). Although acupuncture has been studied for a long time, there is still a lack of knowledge of the effects of acupuncture on the human brain. More research is necessary to better understand how brain activity is affected by acupuncture.

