**Assessments**							
EHQ	X						
Sleep log	X						
SCL-90	X						
PSQI	X						
MoCA			X			X	
WCST			X			X	
DS			X			X	
ESS			X			X	
FS-14			X			X	
EEG-record			X			X	
Adverse events			X	X	X	X	X

*EHQ, Edinburgh Handedness Questionnaire; SCL-90, Symptom Checklist-90; PSQI, Pittsburgh Sleep Quality Index; MoCA, Montreal Cognitive Assessment; WCST, Wisconsin Card Sorting Test; DS, Digit Span of the Wechsler Adult Intelligence Scale; ESS, Epworth Sleepiness Scale; FS-14, Fatigue Scale-14; EEG, Electroencephalogram*.

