## Control Group

Participants in the control group will receive only 36-h ASD but will not receive electroacupuncture treatment.

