## Discussion

The purpose of this trial is to assess the impact of acupuncture on the management of brain cognition control. It is obvious that cognitive function is impaired after sleep deprivation. We intend to compare the effects of time (baseline and 36-h ASD) and intervention (electroacupuncture, sham electroacupuncture and non-electroacupuncture treatment) on executive brain function using a visual Go/No-Go task with simultaneous EEG recordings. Acupuncture is a non-toxic, economical intervention with minimal adverse effects (32) that has been shown to be effective after the therapy (11).

There are several methodological limitations to this study: (1) Due to the characteristics of acupuncture is the non-blinding of the acupuncturist. (2) Only young male subjects will be included; so, the findings may not be generalizable to women and older people. (3) The sample size is small. Despite these limitations, we will use rigorous methodology in this study, and we hope that the trial will help provide new insights into the value of acupuncture and evidence of ERP in executive brain function.

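### The Adverse Events section makes causation by electroacupuncture the condition for recording a non-serious event, which conflicts with its own causality field and with Table 1

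*Protocol article*

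**What the plan says.** The Adverse Events section of the protocol article opens with the recording rule: "Any adverse event resulting from electroacupuncture in participants, such as headache, nausea, dizziness, localized infections, bleeding, or local subcutaneous hematoma, will be recorded". The same sentence commits to assessing and reporting those events. The next sentence lists the details kept for each event, including timing and "correlation with acupuncture, measures taken, and outcomes of adverse events will also be recorded". A last sentence sends serious adverse events to the ethics committee, with no condition on cause.

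Three other places bear on the rule:

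- Control Group section: "Participants in the control group will receive only 36-h ASD but will not receive electroacupuncture treatment".
- Table 1, Assessments: a row labelled "Adverse events" is marked at baseline, 12 h, 24 h, 36 h and 48 h. It is not split by arm and states no limit by cause.
- Follow-Up section: a health check 12 hours after completion asks participants about physical discomfort.

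No passage says that non-serious events are recorded regardless of cause, or that those due to sleep deprivation are.

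**The concern.** The trial imposes two exposures on healthy volunteers, needling and 36 hours awake, and the recording rule names only one of them. The article accepts that the other has effects of its own: it says that "common negative effects of sleep deprivation include feeling too sleepy during the day, accidents from lack of attention, mood changes, and changes in appetite". Several events given as examples in the rule, namely headache, nausea and dizziness, could plausibly come from either exposure.

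If cause has to be settled before an event is entered, the count in each arm depends on a judgement that the acupuncturist or the staff make while knowing the arm. A needling event blamed on tiredness is never entered. A sleep-loss event blamed on the needles is counted against electroacupuncture. The arm that would show the background rate under deprivation alone contributes nothing by rule. What is at stake is whether the trial's harms data can be read across arms. The efficacy result is not at stake.

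**Working it through.** No figure in the plan needs reproducing. The check sets the texts side by side and applies the rule arm by arm.

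**Step 1. Exposures.** These come from the Treatment Group, Placebo Group, Control Group and Blank Group sections. The Placebo Group section does not itself mention sleep deprivation. The Discussion compares electroacupuncture, sham and no treatment across baseline and 36 hours of deprivation, which implies that the sham arm is deprived.

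**Step 2. Which non-serious events meet the opening rule?**

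| Arm | Needles | Current | Deprived | Needling event qualifies | Sleep-loss event qualifies |
|---|---|---|---|---|---|
| Treatment | yes | yes | yes | yes | no |
| Sham | yes | no | yes (implied) | unclear | no |
| Control | no | no | yes | cannot occur | no |
| Blank | no | no | no | cannot occur | cannot occur |

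The sham entry is unclear because that arm has shallow needling with no electrical output. Whether a bruise there results from electroacupuncture depends on how the term is read.

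**Step 3. The rule against the next sentence.** If only events caused by electroacupuncture are entered, the field for relation to acupuncture has the same answer for nearly every entry. The field is informative only if unrelated and doubtful events are also entered. The two sentences therefore imply different populations of events.

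**Step 4. The rule against Table 1.** The row schedules checks at five time points for the trial as a whole. Under the rule, the checks on control participants could never yield a non-serious entry. I do not rely on the baseline column, because the article does not make the time of the first needling session clear.

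**Step 5. What the filtered counts would mean.** In the treatment arm, the recorded count is a + b, where a is needling events attributed to needling and b is sleep-loss events attributed to needling. In the control arm it is 0 by construction. The difference, a + b − 0, omits needling events attributed to sleep loss and includes b with no background count to set against it. It can lie above or below the true excess, and nothing in the recorded data shows which.

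**Step 6. Size.** Sixty participants at 1:1:1:1 gives 60/4 = 15 per arm. Deprived participants: 3 × 15 = 45. Control share: 15/45 = 33%. The Randomization section specifies simple randomization, so arm sizes will vary. With arm size distributed as Binomial(60, 0.25), the central 95% range is 9 to 22. No event rate is assumed.

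**The case against.** The strongest reply is that the exclusive reading is an inference. The opening sentence promises to record one class of event and does not say that others will be left out. The causality field, the Table 1 row and the follow-up question all fit a wider intent: collect in every arm, then rate relatedness. The follow-up check at 36 + 12 = 48 h even coincides with the last Table 1 column. The article also refers, under Data Management and Monitoring, to a standard operating procedure covering the case report form, and that procedure may define adverse events properly.

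Much of this stands. A reader might infer that control participants' events will certainly go unrecorded, or that nobody will ask them. The documents do not support that: staff supervise participants throughout, "there will be two emergency doctors and nurses in the laboratory at all times", and the follow-up question is not confined to needled arms. But signs of wider intent conflict with the opening sentence and do not override it. The follow-up question is a single contact about physical discomfort and is not described as adverse-event recording. This is a stated rule worded too narrowly, not detail left to a fuller document.

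Two other stronger readings should be set aside:

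- A reader might think the trial needs post-enrolment scales for mood, appetite or accidents because the Background names them. Nothing obliges it to have them. Sleepiness is covered by the Epworth scale, which "will be used to evaluate excessive drowsiness during the day", and fatigue by the FS-14.
- A reader might link the rule to the Discussion's remark that "Acupuncture is a non-toxic, economical intervention with minimal adverse effects". That is a cited background statement, not a conclusion this trial sets out to test.

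**Conclusion.** The point holds as a defect in a stated rule. Read literally, the opening sentence of the Adverse Events section excludes every non-serious event in the deprivation-only control arm, about 15 of 45 deprived participants. It also excludes non-serious sleep-loss harms in the treatment and sham arms. It forces attribution before entry for events that either exposure could cause, and it contradicts the sentence that follows it and the Table 1 row. Counts gathered this way could not be compared fairly between arms.

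This rests on three assumptions: that staff follow the opening sentence as written, that the sham arm is sleep-deprived as the Discussion implies, and that arms are near 15 each. The first is the main uncertainty, since the rest of the text suggests wider collection may be meant.

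The reach is limited. Serious adverse events carry no causal condition. The 12-hour discomfort question, the ESS, the FS-14 and the MoCA primary outcome are untouched. The article plans no formal test of harms, and with about 15 per arm any comparison would be descriptive. The wording should be corrected, but it does not threaten the trial's main result.

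**What to change.** Replace the opening of the Adverse Events section with: *Any adverse event in any of the four groups, whatever its cause, at each Table 1 time point, is recorded, assessed and reported.* The listed examples can stay as examples. Then rate relation to needling or electroacupuncture and relation to sleep deprivation as two separate fields, each completed after the event has been entered. Report counts by arm, descriptively.

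The cost is one sentence in the protocol and one extra field on the case report form. No visits are added, because Table 1 already schedules the checks. The small downside is that more minor events will have to be written down.
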